## Abstract

**Background:**

Gait disturbances may appear prior to cognitive dysfunction in the early stage of silent cerebrovascular disease (SCD). Subtle changes in gait characteristics may provide an early warning of later cognitive decline. Our team has proposed a vision-based artificial intelligent gait analyzer for the rapid detection of spatiotemporal parameters and walking pattern based on videos of the Timed Up and Go (TUG) test. The primary objective of this study is to investigate the relationship between gait features assessed by our artificial intelligent gait analyzer and cognitive function changes in patients with SCD.

**Methods:**

This will be a multicenter prospective cohort study involving a total of 14 hospitals from Shanghai and Guizhou. One thousand and six hundred patients with SCD aged 60–85 years will be consecutively recruited. Eligible patients will undergo the intelligent gait assessment and neuropsychological evaluation at baseline and at 1-year follow-up. The intelligent gait analyzer will divide participant into normal gait group and abnormal gait group according to their walking performance in the TUG videos at baseline. All participants will be naturally observed during 1-year follow-up period. Primary outcome are the changes in Mini-Mental State Examination (MMSE) score. Secondary outcomes include the changes in intelligent gait spatiotemporal parameters (step length, gait speed, step frequency, step width, standing up time, and turning back time), the changes in scores on other neuropsychological tests (Montreal Cognitive Assessment, the Stroop Color Word Test, and Digit Span Test), falls events, and cerebrovascular events. We hypothesize that both groups will show a decline in MMSE score, but the decrease of MMSE score in the abnormal gait group will be more significant.

**Conclusion:**

This study will be the first to explore the relationship between gait features assessed by an artificial intelligent gait analyzer and cognitive decline in patients with SCD. It will demonstrate whether subtle gait abnormalities detected by the artificial intelligent gait analyzer can act as a cognitive-related marker for patients with SCD.

**Trial registration:**

This trial was registered at ClinicalTrials.gov (NCT04456348; 2 July 2020).

## Background

Silent cerebrovascular disease (SCD) is the most frequently encountered incidental finding on brain imaging in the elderly [1]. According to previous population-based studies, the overall prevalence of SCD ranges from 8 to 28% in the general elderly population and increases with age [2]. Silent lacunar infarctions were detected in 19.9% of community-dwelling people in China who underwent brain computed tomography (CT)/magnetic resonance imaging (MRI) [3]. A large-scale community-based study in Japan reported a 12% prevalence of autopsy-confirmed silent cerebral infarction [4]. Cerebral microinfarcts were reportedly found in 33% of cognitively normal adults at autopsy in longitudinal studies of brain aging [5]. SCD differs from symptomatic cerebral infarcts in its lack of acute stroke-like nervous function defects; however, subtle deficits in motor, cognitive, mental, and daily living activities are often ignored [2]. The proportions of gait apraxia and progressive cognitive decline in patients with SCD are 27.8 and 38.1%, respectively [6]. Bäzner et al. [7] reported that, compared with healthy controls, the patients with SCD showed a slower cadence, shorter step length, and longer double support phase detected by sensors that worsened progressively after a mean 26 months of follow-up. The Framingham Heart Study [8] showed that individuals with large white matter hyperintensity (WMH) volume performed significantly worse in cognitive domains associated with frontal and medial temporal areas compared with those with less or no WMH volumes in a community-based population of non-demented individuals.

SCD is an independent contributing factor to vascular cognitive impairment and dementia [8] that places a heavy burden on patients, their families, and society. The total payments in the US for people aged 65 and older with dementia were estimated to be $305 billion in 2020 and included long-term care and hospice services [9]. In China, the annual total cost associated with dementia was estimated to be $248.71 billion in 2020 [10]. The effective screening of SCD-related cognitive decline for preventing progression to dementia is challenging. Most neuropsychological scales are time-consuming, and their results are affected by language and education level. Gait is an indicator with advantages such as repetition and reliability. There is increasing evidence that a slow gait occurs in the early stages of dementia and may precede the decline on cognitive tests [11]. An acceleration in gait speed decline reportedly occurred 12.1 years before the onset of mild cognitive impairment [12]. There are many common causes of both cognitive decline and gait impairment, such as lesions in the cerebral cortex [13] (such as the prefrontal cortex), impaired executive function, cardiovascular diseases, and diabetes [14]. Motoric cognitive risk syndrome (MCR), a predementia syndrome, involves a slow gait and cognitive complaints and has the potential to be an alternative method for predicting the risk of cognitive decline in low- and middle-income countries [15]. A meta-analysis showed that the adjusted hazard ratio for MCR predicted the risk of developing incident cognitive impairment in individuals aged 60 years and older reached 2.0 (95% confidence interval [CI], 1.7–2.4) [11].

The current clinical gait assessment mostly depends on visual observations of clinical professionals, and its results are affected by large subjective factors. Professional gait analyzers, such as instrumented walkways and marker-based motion capture systems, are not used widespread in the clinical setting because of their high cost and low portability. Our team proposed a vision-based artificial intelligent gait analyzer for the rapid detection of gait spatiotemporal parameters and walking pattern classification based on videos of the Timed Up and Go Test (TUG) without the use of body markers [16]. By learning the gait diagnosis of three experts, the area under the curve of our intelligent gait analyzer for screening gait abnormalities was 0.96, with an accuracy of 90.14%.

The primary objective of this study is to investigate the relationship between gait features assessed by our artificial intelligent gait analyzer and cognitive function changes in patients with SCD. We hypothesize that patients with SCD who are diagnosed as abnormal gait performance by our artificial intelligent gait analyzer will have greater cognitive decline over 1-year follow-up.

## Methods/design

### Study design

The ACCURATE-2 is a multicenter prospective cohort study that follows the changes in scores of neuropsychological test in patients with SCD to compare the differences between normal gait group and abnormal gait group, and analyzes the correlation between gait spatiotemporal parameters and the changes of neuropsychological test scores.

### Setting

The trial will be conducted at the neurology departments of general hospitals. Fourteen secondary or tertiary hospitals located in the Shanghai and Guizhou areas will be included in this study. All staff members of the trial trained.

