### Assessments

Clinical data such as demographic characteristics, history of present illness, comorbidities, physical examination findings of the nervous system, previous laboratory examination results and imaging findings, and details of falls events in the past year will be collected. The conversations between doctors and patients during data collection will be recorded by voice recorders, and the audio files will only be used for quality control.

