#### Intelligent gait analysis (SAIL system)

The vision-based artificial intelligent gait analyzer we proposed (named SAIL system) includes a data acquisition client and a data analysis server. The data acquisition client consists of a laptop and an RGB-depth camera. The computer application we designed can record the entire TUG test by calling the RGB-depth camera, and upload the video files subsequently to the data analysis server via the network. The data analysis server will detect gait spatiotemporal parameters and walking pattern classification for each patient through the built-in intelligent algorithm and transmits the analysis report back to the data acquisition client through the network.

The TUG videos will be recorded in a bright, clean, and tidy indoor square area (at least 3.8 m × 3.8 m) without any obstruction. A armless chair with standard seat height will be placed on one side, and a visible colored line on the floor will mark a distance of 3 m from the seat. The RGB-depth camera on a 1.2-m-high tripod will be placed 3.8 m away in a vertical line from the midpoint of the footpath. The patients will be required to wear well-fitting trousers and a pair of everyday flat shoes, take off the long coat that reaches the hips, put down the items in their hands, and remove their backpacks before the TUG test. Each participant will be asked to sit on the chair first, stand upon hearing the doctor’s instructions, walk straight to the 3-m mark, turn around, return to the chair, and sit down finally. All participants will complete the TUG test twice at their usual comfortable walking pace, and at least a five-minute break will be given between the tests. Participants can practice 1–2 times to familiarize with the walking test requirements.

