#### Neuropsychological evaluation

Participants will be evaluated on the following neuropsychological tests by trained doctors:Mini-Mental State Examination (MMSE), Chinese version translated by Mingyuan Zhang: evaluates time and place orientation, attention and calculation, recall, language, and copying. Scores range from 0 to 30 points, with a lower score indicating worse cognitive function.Montreal Cognitive Assessment (MoCA), Beijing version: evaluates visual-spatial ability, executive function, naming, memory, attention, language, abstraction, and orientation. Scores range from 0 to 30 points, with a lower score indicating worse cognitive function.The Stroop Color word test (CWT), Huashan version: evaluates semantic activation, dominant response inhibition, attention, working memory, and information processing speed. The time spent in each card and the number of errors will be recorded. A longer time cost or more errors indicate worse cognitive function.The digit span test (DST), a subtest of the Chinese version of the Wechsler Adult Intelligence Scale-Revised: evaluates immediate memory and attention. A shorter string of repeated numbers indicates worse cognitive function.

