### Statistical analysis

All measurement data will be tested using the Shapiro-Wilk normality test. Normally distributed continuous measurement data will be expressed as mean and standard deviation, while non-normally distributed measurement data will be expressed as median and interquartile range. The t-test, Wilcoxon signed-ranks test, repeated measures t-test, or linear generalized model will be used to compare measurement data. The enumeration data will be expressed as a composition ratio or rate. The chi-square test or Fisher exact method will be used to compare enumeration data. Pearson linear correlation analysis or Spearman correlation analysis will be performed for correlation analysis. Survival will be estimated using a Kaplan-Meier survival curve. The propensity score matching method will be used to minimize the influence of other confounders. Subgroup analyses will include region and hospital levels. All cases with missing values will be deleted. A significant difference will be identified *P* < 0.05.

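### No stated method ensures that the gait contrast in MMSE change is separated from hospital; site is named only for subgroup analyses

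*Protocol article*

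**What the plan says.** The Setting section states "Fourteen secondary or tertiary hospitals located in the Shanghai and Guizhou areas will be included in this study". Under Grouping and follow-up plan design, patients are not randomised: the gait analyzer assigns each to normal or abnormal gait at baseline. The primary outcome is the one-year change in MMSE.

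The Statistical analysis section gives the comparison methods as follows: "The t-test, Wilcoxon signed-ranks test, repeated measures t-test, or linear generalized model will be used to compare measurement data". Gait parameters and score changes, whose correlation is part of the Study design, are handled by Pearson or Spearman correlation. On confounding it says "The propensity score matching method will be used to minimize the influence of other confounders", without listing covariates. The one mention of site is "Subgroup analyses will include region and hospital levels". Since Setting distinguishes secondary from tertiary hospitals, "hospital levels" most naturally means that two-way split, so the individual hospital is probably not even a subgroup factor.

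**The concern.** This is an observational contrast across 14 hospitals in two regions. Case mix, the pace of decline and the stability of raters between visits may differ by hospital, and so may the share of patients classed as abnormal gait. If these move together, a pooled comparison credits part of a hospital difference to gait. Subgroup analyses by region and hospital level describe the effect within strata; they do not adjust the main estimate. A t-test, a rank test and a simple correlation have no place for a hospital term. The planned difference is only 0.2 MMSE points, so a small hospital effect could matter.

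**Working it through.** **The plan's own figure.** Inputs from the Sample size section: decline 0.5 (SD 0.5) versus 0.7 (SD 1.2), abnormal to normal 1:2, 90% power, alpha 0.05 (taken as two-sided), 20% dropout.

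- n(abnormal) = (1.2² + 0.5²/2) × (1.960 + 1.282)² / 0.2² = 412 after rounding up; n(normal) = 824; total 1,236.
- Divided by 0.8: 515 + 1,030 = 1,545. The stated 550 + 1,050 = 1,600 is 3.6% larger (1,600/1,545), on the safe side.
- After 20% dropout, 440 + 840 = 1,280 completers remain, with power of about 92%.

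The calculation is broadly consistent with its inputs. It treats patients as independent and makes no allowance for hospital.

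**Standard error of the planned contrast.** SE = √(0.5²/840 + 1.2²/440) = 0.060.

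**One bias scenario (assumed; the documents give no regional figures).** One third of patients come from a region with 50% abnormal gait, against 25% elsewhere. Overall prevalence is 1/3 × 0.50 + 2/3 × 0.25 = 1/3, matching the planned 1:2 ratio. Then:

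- share of the abnormal group from that region = (1/3 × 0.50)/(1/3) = 0.50
- share of the normal group from that region = (1/3 × 0.50)/(2/3) = 0.25
- spurious difference = extra regional decline × (0.50 − 0.25)

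| Extra decline in that region | Spurious difference | Share of 0.2 | In SE units | False positives, no true effect |
|---|---|---|---|---|
| 0.1 | 0.025 | 13% | 0.42 | 7% |
| 0.2 | 0.050 | 25% | 0.84 | 13% |
| 0.3 | 0.075 | 38% | 1.25 | 24% |

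The last column is P(|Z + shift| > 1.96), with the shift in SE units. The 0.3-point gap has between-region variance 0.3² × 1/3 × 2/3 = 0.020. The within-group variance is 2/3 × 0.5² + 1/3 × 1.2² = 0.647. The implied outcome ICC is 0.020/0.667, about 0.03.

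**A wider range, by simulation.** 14 hospitals × 91 completers, no true gait effect, the planned SDs, 1,500 runs per scenario. Assumed: ICC of MMSE change between hospitals of 0.01 to 0.10; mean abnormal-gait prevalence 1/3 with between-hospital SD of 0, 0.10 or 0.15; correlation of prevalence with hospital decline of 0 or 0.5. The adjusted analysis uses hospital fixed effects and robust standard errors.

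| Prevalence across hospitals | Tracks decline? | Mean spurious difference, plain test | Type I error, plain test | Type I error, hospital-adjusted |
|---|---|---|---|---|
| Equal | – | about 0 | about 5% | 4–6% |
| SD 0.10–0.15 | No | about 0 | 5–7% (ICC 0.01–0.05); 8–12% (ICC 0.10) | 5–6% |
| SD 0.10–0.15 | Yes, 0.5 | 0.02–0.08 | 7–30% | 5–7% |

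With hospital in the model the mean spurious difference was at most 0.005 points in every scenario, and the standard error stayed at about 0.06. Simulation error on a 5% rate is about ±1 point.

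**The case against.** The strongest reply is that a journal article need not list model terms. The linear generalized model could carry hospital, and the propensity score could include it; the analysis plan that would say so is not shown. That stands. A reader might infer that hospital will be ignored altogether, and the article does not support that. What it does support is narrower: most of the methods it names cannot take a hospital term, the one that can is an unspecified alternative, and matching on a pooled score does not by itself produce pairs from the same hospital. Nor does two-group matching have an evident role in the correlations of gait parameters with score change.

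A second reply is that the Background sentence "Most neuropsychological scales are time-consuming, and their results are affected by language and education level" concerns score level, whereas the outcome is a within-patient change. That also stands. A reader might infer that stricter scoring at some hospitals biases the contrast; a constant offset largely cancels. What remains is differing decline, rater drift or a change of rater.

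Third, there are safeguards. The article says "Participants will be evaluated on the following neuropsychological tests by trained doctors"; conversations during data collection are recorded and "the audio files will only be used for quality control"; and gait is classified centrally: "The data analysis server will detect gait spatiotemporal parameters and walking pattern classification for each patient through the built-in intelligent algorithm". These reduce rater and classification differences between sites. They do not remove differences in case mix or pace of decline.

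Finally, a reader might apply the usual cluster design effect, 1 + (m − 1) × ICC, which at ICC 0.05 and m = 91 gives 1 + 90 × 0.05 = 5.5. It does not apply, because gait class varies within hospitals. With equal prevalence the simulated plain standard error was correct even at ICC 0.10.

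**Conclusion.** The point holds in a limited form. As stated, the methods do not ensure that the primary contrast, or the gait-parameter correlations, are separated from hospital, and the subgroup analyses do not fill that gap. The consequence depends on facts that the documents do not give. With equal abnormal-gait prevalence across hospitals there is neither bias nor inflation. With varying prevalence unrelated to decline there is no bias, and type I error is about 5–12%. With prevalence that tracks decline, the spurious difference is 0.02 to 0.08 points against a planned 0.2, with type I error of 7–30%. All ICCs, prevalence spreads and regional gaps are assumptions. It would go too far to say that the estimate will be biased or that p-values will be too small. The risk is possible, material against so small an effect, and cheap to remove.

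**What to change.** Make the primary analysis of MMSE change a linear model with gait group and hospital as a fixed effect, using robust standard errors because the planned SDs differ (0.5 and 1.2). Replace the pooled gait-parameter correlations with the same hospital-adjusted regression. If propensity matching is kept, match within hospital. Examine region and hospital level by their interaction with gait group, in place of separate subgroup results.

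The cost is 14 − 1 = 13 degrees of freedom out of about 1,280, and possibly some unmatched patients if matching is done within hospital. No new data are needed.

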### Participants

In this study, patients with SCD aged 60–85 years will be consecutively recruited and agree to participate for at least 12 months. Neurologists will identify eligible patients by browsing outpatient cranial MRI images. Patients will be informed about the research contents, and those willing to participate will be given a written informed consent form to sign. After recruitment, suitable patients will be selected according to the inclusion and exclusion criteria.

#### Inclusion criteria

Aged 60–85 years.Diagnosed with SCD according to the 2016 statement issued by the American Heart Association and the American Stroke Association [17]:

(A)Absence of clinically recognized acute stroke symptoms.(B)Cranial MRI taken in the past 1 year having shown one of the following (according to STRIVE [18]):Lacunes of presumed vascular origin: defined as a subcortical, round, or ovoid fluid-filled cavity with a diameter of 3–15 mm showing a low central signal and irregular marginal high signal on T2 fluid-attenuated inversion recovery (T2-FLAIR). The central signal is similar to that of cerebrospinal fluid, and the distribution is consistent with the blood supply area of the perforating artery. Fazekas scores should be ≥2 points.WMH of presumed vascular origin: defined as hyperintensity on T2-FLAIR in the white matter area (periventricular or subcortical), the signal of which differs from cerebrospinal fluid. Fazekas scores should be ≥2 points.Microbleed: defined as a small round area devoid of signal with associated blooming on susceptibility weighted imaging or T2-weighted imaging generally 2–10 mm in diameter. Microbleed lesion number should be ≥5.
(3)Conscious and able to finish all neuropsychological test.(4)Ability to stand and walk independently without waking aids, and complete the intelligent gait assessment.(5)Sign the informed consent form.

#### Exclusion criteria

Definitively diagnosed as demyelination disease, leukodystrophy, space-occupying lesions, or autoimmune encephalitis, etc.Definitively diagnosed as Parkinson’s disease, normal pressure hydrocephalus, inner ear disease, subacute combined degeneration, peripheral neuropathy, osteoarthritis, or lumbar disease, etc.Definitively diagnosed as Alzheimer’s disease, frontotemporal dementia, or Lewy body dementia, etc.Previous history of severe neurological diseases such as cerebral trauma, epilepsy, alcoholic encephalopathy, or myeleterosis, etc.Severe cardiovascular complications and inability to tolerate the assessment.Severe visual impairment, severe hearing impairment, aphasia, severe cognitive dysfunction, severe gait, balance disturbance and inability to complete the cognition scale and intelligent gait assessments.Refusal to participate in the study.Other anomalies not specified that the researchers considered inappropriate for inclusion in this study.

### Assessments

Clinical data such as demographic characteristics, history of present illness, comorbidities, physical examination findings of the nervous system, previous laboratory examination results and imaging findings, and details of falls events in the past year will be collected. The conversations between doctors and patients during data collection will be recorded by voice recorders, and the audio files will only be used for quality control.

#### Intelligent gait analysis (SAIL system)

The vision-based artificial intelligent gait analyzer we proposed (named SAIL system) includes a data acquisition client and a data analysis server. The data acquisition client consists of a laptop and an RGB-depth camera. The computer application we designed can record the entire TUG test by calling the RGB-depth camera, and upload the video files subsequently to the data analysis server via the network. The data analysis server will detect gait spatiotemporal parameters and walking pattern classification for each patient through the built-in intelligent algorithm and transmits the analysis report back to the data acquisition client through the network.

The TUG videos will be recorded in a bright, clean, and tidy indoor square area (at least 3.8 m × 3.8 m) without any obstruction. A armless chair with standard seat height will be placed on one side, and a visible colored line on the floor will mark a distance of 3 m from the seat. The RGB-depth camera on a 1.2-m-high tripod will be placed 3.8 m away in a vertical line from the midpoint of the footpath. The patients will be required to wear well-fitting trousers and a pair of everyday flat shoes, take off the long coat that reaches the hips, put down the items in their hands, and remove their backpacks before the TUG test. Each participant will be asked to sit on the chair first, stand upon hearing the doctor’s instructions, walk straight to the 3-m mark, turn around, return to the chair, and sit down finally. All participants will complete the TUG test twice at their usual comfortable walking pace, and at least a five-minute break will be given between the tests. Participants can practice 1–2 times to familiarize with the walking test requirements.

On the data analysis server, the pose estimation algorithm will be used to identify the human key body surface points in each frame of the TUG video (such as head, shoulder, elbow, wrist, hip, knee, and ankle), and process the data by filtering and double-threshold signal-detection methods to calculate the six gait spatiotemporal parameters, including step length, gait speed, step frequency, step width, standing up time, and turning back time. Step length is defined as the average distance from the landing of one foot to the subsequent landing of the other foot, and a shorter step length will indicate worse gait performance. Gait speed is defined as the average velocity of walking during the straight parts of the TUG test, and a slower gait speed will indicate worse gait performance. Step frequency is defined as the average steps taken per second, and a slower step frequency will indicate worse gait performance. Step width is defined as the depth distance between two heels, and a wider step width will indicate a worse gait balance. Standing up time is defined as the time interval from the beginning of the video to the timepoint when the height of two shoulders reach the highest, which includes reaction times and stand-up action times, and a longer time will indicate worse gait performance. Turning back time is defined as the time between the start and end of the shoulder twisting, and a longer time will indicate worse gait performance. The native Bayes classifier that has learned the expert gold standard before will be applied to classify gait performance as normal or abnormal.

